#### Perceived Social Support Questionnaire

The Social Support Questionnaire was adapted from the Perceived Social Support (Fragebogen zur Sozialen Unterstützung) 6-item scale developed by Kliem et al [54] and Lin et al [55]. This German tool evaluates adolescents’ capacity to recognize the availability of assistance from friends, family, and peers in times of need. For this study, minor adjustments were made to the questionnaire with the authors’ permission while preserving its core purpose. The scale demonstrated high reliability, with an internal consistency (Cronbach α) of 0.90.

#### Suicide Literacy

Suicide literacy, a vital component of mental health literacy, encompasses knowledge of suicide’s warning signs, causes, risk factors, and preventive measures [56]. The Literacy of Suicide Scale, developed and evaluated by McGillivray et al [20], includes 26 items assessing suicide literacy across 4 dimensions: signs and symptoms (5 items), causes and triggers (10 items), risk factors (7 items), and treatment and prevention (4 items) [56]. Each question has a correct answer, scored as 1 point, while incorrect or “I don’t know” responses score 0. In this study, 1 question was removed, resulting in a 25-item scale with scores ranging from 0 to 25, where higher scores reflect better suicide literacy.

#### Attitude Toward Help-Seeking Behavior

The Attitude Toward Seeking Professional Psychological Help Scale by Fischer and Farina [57] will be used to assess participants’ attitudes toward seeking help regarding mental health problems. This tool consists of 10 items rated on a Likert scale ranging from 1 (disagree) to 4 (agree). The total score, obtained by summing individual item scores, reflects a positive attitude toward seeking psychological help. With reliable psychometric properties, the instrument has a reliability index ranging from 0.80 to 0.86 [58].

#### Life Attitudes Schedule

The Life Attitudes Schedule–Short Form by Rohde et al [59] is a 24-item binary measure assessing thoughts and behaviors associated with an increased risk of future suicide ideation, attempts, and completions. Participants respond with either true (1) or false (0), and the scores are summed up from a scale score ranging from 0 to 24 to create a total scale score. Higher scores reflect greater engagement in life-enhancing behaviors, while lower scores indicate increased participation in life-threatening behaviors. The scale has exhibited commendable internal consistency, with a Cronbach α of 0.78 [60], and demonstrated excellent construct validity with regard to history of suicide attempts, depressive symptoms, and impulsivity [61].

#### Depression, Anxiety, and Stress Level

The depression, anxiety, and stress levels will be assessed by the DASS-21 questionnaire, which was translated into Urdu, the national language of Pakistan, by Gillani et al [62], to assess the perceived stress levels and psychological well-being of the Pakistani population in Islamabad. Its internal consistency was assessed, revealing a Cronbach α of 0.94. DASS-21 will serve as a screening tool, evaluating stress, depression, and anxiety over the past week through 21 items, each consisting of a set of 7 questions. Responses on the Likert scale range from 0 to 3, where “never” corresponds to 0, “sometimes” to 1, “frequently” to 2, and “always” to 3. [63]. Depression, anxiety, and stress levels of participants will be assessed using predefined cutoff values as follows: depression score of less than 6, anxiety score of less than 5, and stress score of less than 9, in accordance with the DASS-21 guidelines [64].

#### Adaptive Coping Strategies

The Brief–Coping Orientation to Problems Experienced questionnaire, a validated 28-item self-report tool developed by Carver [65], assesses both effective and ineffective coping strategies in response to stressful life events. Participants rate their engagement in each strategy on a scale from 1 (not doing at all) to 4 (doing a lot). The questionnaire encompasses 14 coping strategies, including self-distraction, active coping, denial, substance use, emotional support, instrumental support, behavioral disengagement, venting, positive reframing, planning, humor, acceptance, religion, and self-blame. Scores for each coping style range from 2 to 8, with higher scores indicating a greater inclination toward using that specific coping mechanism [66]. The tool has demonstrated an internal reliability of 0.86 [67].

#### Self-Efficacy

Self-efficacy will be measured using a 10-item Generalized Self-Efficacy Scale, which gauges individuals’ optimistic beliefs about their competence, encompassing determination, problem-solving, and coping skills [68]. Responses range from 1 (not at all true) to 4 (exactly true). The Urdu translation was already done by Mansoor and Ahmad [69].

### Feedback and Evaluation

At the conclusion of the workshop, the participants will be provided with a feedback questionnaire to freely share their thoughts about this session as well as comments on suicidal ideation. This feedback questionnaire has been adapted and modified from a previous study conducted in Pakistan [70]. All participants will be asked to complete a feedback questionnaire assessing several aspects on a Likert scale. These include the comprehensibility of the language used, relevance of the content, enjoyment of the session, effectiveness of strategies used, usefulness of the session, clarity and simplicity of activities, excellence of the overall training, practicality of the session, appropriateness of its duration, and inviting comments and suggestions for improvement [71].

### Reliability and Validity of Tools

The appropriateness and relevance of the tool in the Pakistani context will be checked by experts. Psychologists will assess the validity through the validation of the content for clarity and relevance. The tools will be translated into Urdu by a linguistic expert. The Urdu versions of the questionnaires, alongside the English version, will be distributed to 4 mental health experts for assessment of language clarity, word choice and order, and representativeness of the construct. Feedback provided by the experts will be integrated into the questionnaires. In addition, back translation into English will be conducted by 4 experts. The content validity will be measured by following a standard protocol of content validity index (CVI) scores.

As mentioned by Yusoff [72], the researcher will seek definitive evaluation evidence for the tool. A rubric will be used, with a Likert scale, to assess relevance (1=not relevant, 2=somewhat relevant, 3=pretty relevant, and 4=very relevant) and clarity (1=not clear, 2=somewhat clear, 3=quite clear, and 4=very clear). Ratings of 1 and 2 will prompt consideration for potential adjustments, while evaluations of 3 and 4 will be considered acceptable. The evaluation panel will make recommendations for alterations, resulting in a clarity score of 0.95 and a relevance score of 0.86, according to the CVI analysis. Moreover, for determining the tool’s reliability, Cronbach α will be used. Pilot testing, involving 10% (4/40) of the sample size, will be conducted to ensure reliability. The resulting CVI and Cronbach α coefficient will provide statistical confirmation regarding the reliability, validity, and clarity of the study questionnaire.

### Data Collection

The principal investigator has received safeTALK training from LivingWorks and will train data collectors for the data collection process. The training includes presentations, videos, discussions, questions, and role-play. All participants will receive identical training at no expense, with no alterations in the delivery or content. Demographic information will be solely collected from participants who provide consent and agree to complete both pre- and posttraining surveys; however, the analysis will be restricted to data furnished by those who complete the surveys based on per-protocol analysis [73]. To promote data quality, study personnel will be trained in the administration of these instruments, and procedures for double data entry, verification, and management will be implemented to ensure accuracy and completeness. Data collection forms will be securely stored, with access limited to authorized personnel to maintain confidentiality [74]. Strategies to promote participant retention and complete follow-up will include clear communication about the study’s importance and duration during the consent process, maintaining regular contact with participants and ensuring the study procedures are convenient and acceptable. For participants who discontinue or deviate from intervention protocols, efforts will be made to collect available outcome data to allow for intention-to-treat analysis, where feasible.

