### Null Hypotheses

The hypotheses are as follows:

Hypothesis 1—suicidal ideation risk among school-going adolescents in GB is similar at baseline and 8 weeks following the implementation of the suicide prevention program.Hypothesis 2—Compared to baseline, there is no mean difference in suicide awareness, suicide literacy, and attitude to seek help after 8 weeks of participation in a suicide prevention program (RAAHI and safeTALK) among school-going adolescents.Hypothesis 3—Compared to baseline, there is no difference in the mean score of depression, adaptive coping strategies, and self-efficacy after 8-week suicide prevention programs (RAAHI and safeTALK) among school-going adolescents.

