#### Exclusion Criterion

Adolescents who will be absent or sick on the day of data collection and intervention will not be included in the study.

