### Data Analysis

Statistical analysis will be conducted using SPSS (version 26; IBM Corp). The normality of data distribution will be assessed, and continuous variables will be summarized using means and SDs (for symmetrical distributions) or medians and IQRs (for skewed distributions), while categorical variables will be presented as frequencies and proportions. Changes in continuous variables (suicidal awareness, suicide literacy, and help seeking) over time will be analyzed using a linear mixed-effects model, and the binary outcome of current suicidal ideation will be analyzed using a population-averaged generalized estimating equation. Linear regression will be used to estimate β coefficients and 95% CIs for predictor variable effects. To compare pre- and postintervention scores on the Literacy of Suicide Scale, a paired samples 2-tailed *t* test will be used, and repeated measures ANOVA with a Bonferroni post hoc test will also be calculated. All primary and exploratory findings will include effect sizes, CIs, and significance levels. While exploratory subgroup analyses may be conducted, they will be clearly identified and interpreted cautiously due to their post hoc nature. Any deviations from the original analysis plan will be justified, and results will be presented with transparency in well-organized tables and figures, including appropriate titles, legends, and footnotes. Data distribution will be further assessed using histograms and the Shapiro-Wilk test to confirm normality assumptions, and the homogeneity of variances will be verified using the Levene test. Any anomalies in the data will be discussed in relation to potential methodological or contextual factors.

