#### Consent for Publication

Participants will be asked for their consent during the data collection process, explaining that the collected data may be used for the dissemination of scientific knowledge. However, no personal names or specific identifying information will be revealed in the published material to ensure confidentiality and privacy (Multimedia Appendix 2). Participants will also be requested to give permission to publish any relevant data or materials without disclosing their identity.

Participation in this study is entirely voluntary. The research team, composed of psychologists and the principal investigator, will secure informed consent from parents or guardians after clearly explaining the study’s objectives during sessions at the school, allowing ample time for inquiries and ensuring a pressure-free decision environment. Students will provide their own informed assent (Multimedia Appendix 3). It is crucial that participants know they can withdraw from the study at any stage without facing any disadvantage; should they choose to withdraw, their collected information will be removed from the study analysis. Currently, no ancillary studies requiring separate consent for data use are planned.

Maintaining participant confidentiality is a priority throughout the research process—before, during, and after data collection. Personal information will be gathered securely, and anonymity will be protected by using unique identification codes and pseudonyms, effectively separating personal identities from research data. All electronic data files are password protected, and any reports generated will exclude identifying details such as names. While the study presents minimal potential risks, if a participant’s results suggest potential susceptibility, this information will be confidentially discussed with their parents (only after obtaining explicit parental consent) to facilitate a referral for further assessment. This sensitive information will not be disclosed to school authorities. The psychologists assisting with data collection are prepared to identify and offer support for any immediate distress participants might experience.

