### Ancillary and Posttrial Care and Referral Mechanism

The data will be collected by trained psychologists, and all the identified cases will be referred to a counselor who will also be hired for the study, so they can refer the extreme cases for further treatment. The employed counselors will be on hand at the study sites for data collection and intervention. The cases presenting extreme suicidal ideation thoughts will be referred for follow-up. The screening and referral expenses of the participants will be borne by the study [71]. The attendees will also be informed about the resources that are accessible, such as the hotlines of the suicide prevention organizations operating in Pakistan.

For this trial, the criteria for discontinuing or modifying allocated interventions for a participant will include a participant’s explicit request to withdraw, the emergence of any unforeseen serious adverse events related to the intervention, or if the participant’s mental state significantly deteriorates, requiring a different level of care. Strategies to improve adherence to the intervention protocol will involve clear communication of the program’s duration and expectations during the informed consent process; regular engagement with participants, which may include follow-ups; and ensuring the intervention is delivered in a manner that is acceptable and feasible for the participants. Participants will be informed about any permitted or prohibited concomitant care or interventions during the trial period to avoid any potential confounding factors.

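### The protocol names two incompatible analysis sets without saying which is primary, and its completer rule may bias the change in suicidal ideation, plausibly toward benefit

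*Protocol article*

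**What the plan says.** Three statements in the protocol article decide whose data enter the analysis.

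- **Data Collection, completer rule:** "the analysis will be restricted to data furnished by those who complete the surveys based on per-protocol analysis".
- **Data Collection, last sentence,** on participants who discontinue or deviate from the intervention: "efforts will be made to collect available outcome data to allow for intention-to-treat analysis, where feasible".
- **Consent for Publication:** "should they choose to withdraw, their collected information will be removed from the study analysis".

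Two further statements bear on who might be lost. The Exclusion Criterion reads "Adolescents who will be absent or sick on the day of data collection and intervention will not be included in the study". The section on ancillary and post-trial care lists grounds for discontinuing or modifying the intervention, among them "if the participant’s mental state significantly deteriorates, requiring a different level of care".

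The primary research question is suicidal ideation. Hypothesis 1 is that "suicidal ideation risk among school-going adolescents in GB is similar at baseline and 8 weeks following the implementation" of the programme. Data Analysis says that "the binary outcome of current suicidal ideation will be analyzed using a population-averaged generalized estimating equation" (GEE). That section names no analysis set. Study Design states that there is no control group. It promises sensitivity analyses for biases such as maturation and historical events, and does not mention missing outcomes. Sample Size plans for 20% dropout and 267 students.

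**The concern.** A per-protocol completer set and an intention-to-treat set are different populations and can give different answers. With both promised and neither called primary, the choice can be made after the data are seen. The withdrawal rule also makes full intention-to-treat impossible, because it deletes the baseline and immediate post-test records of those who withdraw as well as stopping later collection.

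The choice matters more here than in a two-arm trial. No comparison group suffers the same loss, so any link between loss and worsening passes directly into the estimated programme effect. A student who feels worse may well be more likely to miss the 8-week survey or to withdraw. If so, the completers would show a fall in ideation even if the programme did nothing, and the protocol intends its results to support scale-up in schools.

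**Working it through.** **1. The statements side by side**

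| Student | Completer rule | Intention-to-treat sentence | Withdrawal rule |
|---|---|---|---|
| Attends workshops, misses the 8-week survey | Out | In, on available data | Not addressed |
| Stops the workshops, completes all surveys | Out, if per-protocol has its usual meaning | In | Not addressed |
| Withdraws after the immediate post-test | Out | In, on data already collected | All data removed |

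No student in these rows is treated consistently by the first two statements. In the third row the withdrawal rule overrides intention-to-treat.

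**2. When a completer analysis is biased**

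Let d be the share lost, C the change in completers and L the change in those lost. The full-cohort change is F = (1 − d)C + dL, so C − F = d(C − L). Bias needs C and L to differ. A higher baseline risk among those lost does not by itself bias the paired change in completers.

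With F = 0, C = −dL/(1 − d). At d = 0.20:

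- L = +10 points: C = −0.20 × 10/0.80 = −2.5 points (spurious fall).
- L = +20 points: C = −5.0 points.
- L = 0: no bias.
- L = −10 points (those lost improve): C = +2.5 points (spurious rise).

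The documents give no value for L.

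**3. How often a null programme would look effective**

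From the protocol: N = 267, 20% loss, α = 0.05 (taken as two-sided). Assumed, with no source in the documents: 10% of students newly develop ideation, 10% lose it, and worseners are lost k times as often as everyone else. Total loss is held at 20%, so the loss rate in others is p = 0.20/(0.9 + 0.1k) and in worseners kp. Each group starts with 267 × 0.10 = 26.7 students, and about 267 × 0.80 = 213.6 complete.

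The spurious fall is (improvers kept − worseners kept)/213.6. The test is McNemar's, z = (improvers − worseners)/√(improvers + worseners), a simple stand-in for the planned GEE. The last column is from simulation.

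| k | Loss, others | Loss, worseners | Improvers kept | Worseners kept | Spurious fall (points) | False benefit |
|---|---|---|---|---|---|---|
| 1 | 20.0% | 20.0% | 21.4 | 21.4 | 0 | about 3% |
| 1.5 | 19.0% | 28.6% | 21.6 | 19.1 | 1.2 | about 6% |
| 2 | 18.2% | 36.4% | 21.8 | 17.0 | 2.3 | about 12% |
| 3 | 16.7% | 50.0% | 22.3 | 13.4 | 4.2 | about 32% |

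Hand check at k = 3: z = (22.25 − 13.35)/√35.6 = 1.49, and P(Z > 1.96 − 1.49) is about 0.32. The nominal rate in the direction of benefit is 2.5%.

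**4. Why changing the set is not enough**

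Suppose 20% are lost, nobody changes, baseline ideation is 60% in those lost and 35% in completers (assumed). All students at baseline give 0.80 × 0.35 + 0.20 × 0.60 = 40%, while the 8-week completers give 35%. Comparing the two shows a spurious fall of 5 points, where the paired completer change is zero. A GEE with an independence working correlation on all available data makes this comparison, so the enlarged set needs a method valid under missing at random.

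**The case against.** The strongest reply is that the documents do not establish that loss is related to worsening, and that several tempting inferences go further than the text.

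- **Deteriorating students leave the analysis.** A reader might infer this from the clause on "mental state significantly deteriorates, requiring a different level of care". That clause concerns the intervention, not follow-up, and Data Collection says outcome data will still be sought from those who discontinue. The intervention is two workshops, so a student who worsens afterwards has no sessions left to stop. What remains is narrower: a student whose workshops were stopped would be off protocol, and the completer rule as worded would then exclude that student even with full data.
- **The exclusion criterion removes enrolled students.** It most naturally means the baseline and workshop day, since the pretest comes just before training and the first post-test just after. A student absent then never enters the cohort, which affects generalisability and not the within-person change. With three data-collection points, however, the wording does not rule out applying it to the 8-week visit.
- **The bias is large.** If only worseners were lost, a quarter of them or half of them, false benefit would be about 16% or about 57%. Those scenarios imply total losses of only 2.5% and 5%, with no one else dropping out. At the planned 20%, losing half the worseners gives 32%.
- **The mixed model is wasted.** The completer rule does discard partial records the mixed model could use, but that model serves awareness, literacy and help seeking, which are secondary.

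It is also fair that imputation details are usually left to an analysis plan. The finding does not rest on their absence. It rests on an analysis set that the article states, and states inconsistently.

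**Conclusion.** The defect is in the text. Data Collection gives two incompatible analysis sets with no primary, and the withdrawal rule undercuts one of them. In a single-group comparison of baseline with 8 weeks, the completer rule may bias the ideation result, plausibly toward benefit, if students who worsen are lost more often than others.

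A reader might conclude that the result is biased toward benefit. The documents do not support that: they hold no data on how change differs between completers and those lost, and equal loss leaves the error rate near its nominal level. Under the assumptions above, moderate differential loss (1.5 to 2 times) raises false benefit to about 6% to 12%, and threefold loss to about 32%. These figures depend on the assumed 10% transition rates and on the loss pattern, and are illustrations, not predictions.

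**What to change.** 1. Name one primary analysis set: all enrolled students with a baseline (T1) assessment, analysed on all available T1 to T3 data whatever their workshop attendance or discontinuation.
2. State that the exclusion criterion applies only before enrolment, and that absence at T2 or T3 is missing data.
3. Keep data collected up to withdrawal unless the participant asks for deletion, and align the consent and assent text with this.
4. Handle missing ideation outcomes with a method valid under missing at random, for example multiple imputation before the GEE. This corrects only for what earlier measurements predict. Loss that depends on unseen 8-week status would remain, so reasons for loss should be recorded and reported.
5. Report per-protocol completers as a labelled sensitivity analysis.

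The criteria for discontinuing or modifying the intervention need no change for this purpose. The article need only say that they do not end follow-up or remove data.

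The cost is protocol and consent wording with ethics notification, modest extra analysis, and possibly a less favourable estimate. Consent and follow-up changes help only if made before the 8-week data are complete. The choice of primary set should be fixed before the outcomes are examined.
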